### Analyses

On the basis of an intention-to-treat analysis, differences in outcome measures between the intervention group and control group are calculated with 95% confidence intervals. In addition, per protocol analyses that only include participants that attended three or more group sessions will be performed. In the unlikely case that, in spite of randomisation, an important prognostic factor is unequally distributed over groups, the analysis will be adjusted. Analysis of (co)variance, linear and logistic regression will be used to determine the effect of the intervention on each of the outcome measurements.

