### Data collection and outcome measures

Outcome measures will be assessed at baseline (T0) and directly after the intervention at six months (T1) and at twelve months (T2) by means of self-reported questionnaires. The primary outcome is diabetes-related distress. Health-related quality of life, well-being, and self-management behaviour will be reported as secondary outcomes. Perceived social support will be considered a process measure to evaluate whether the intervention will in fact lead to an increase in the providing and receiving of social support. The questionnaire will also include questions regarding patients’ sociodemographic and illness characteristics, for example sex, age, material status, ethnic origin, education, treatment of T2DM and complications.

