### Sample size

The sample size per group is calculated as ((Z_(1 - *α*/2)_ + Z_(1 - *β*)_)^2^ × 2*σ*^2^)/*δ*^2^, where δ is the minimal important difference to be shown between the means of both groups (intervention vs. control), σ is the standard deviation, α is the type I error rate, and β is the type II error rate. α is set at 0.05 (double-sided, Z_α_ =1.96) and power at 80% (*β* = 0.20, Z_
*β*
_ = 0.84). The proposed trial is designed to detect a clinically relevant change in diabetes-related distress. No consensus exists about minimal important differences (MID) of distress measured with the PAID. Therefore, we set the MID (δ) at half of a standard deviation. This is a well-known solution when scores have no direct interpretation and no clinical results exist to determine a relevant percentage. In diabetes patients, the standard deviation (SD) of PAID (scores transformed to 0-100) was 20 points [4]. This leads to a sample size of 63 per group required to find a difference of 10 points (0,5 SD). Allowing for an attrition rate of 20% from initial recruitment, 76 subjects in each arm are required (i.e. 152 participants in total).

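### The methods named for the intention-to-treat analysis do not by themselves keep participants with missing PAID scores in the comparison; a longitudinal mixed model would make better use of scores already collected

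*Protocol article*

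**What the plan says.** - **Population.** The Analyses section of the protocol article says: "On the basis of an intention-to-treat analysis, differences in outcome measures between the intervention group and control group are calculated with 95% confidence intervals". It adds a per-protocol analysis restricted to people who came to at least three sessions.
- **Methods.** The same section says: "Analysis of (co)variance, linear and logistic regression will be used". Adjustment is foreseen only if an important prognostic factor happens to be unevenly spread over the arms. Adjustment for baseline PAID is not fixed, and no repeated-measures or likelihood-based longitudinal model is named.
- **Data.** Under Data collection and outcome measures, PAID is collected at baseline (T0) and then "directly after the intervention at six months (T1) and at twelve months (T2) by means of self-reported questionnaires".
- **Expected loss.** The Sample size section says: "Allowing for an attrition rate of 20% from initial recruitment, 76 subjects in each arm are required". The 20% is one overall figure, not split by arm or by questionnaire.
- **Burden.** The Intervention section asks for a two-hour session each month for six months. The Control group section offers one educational meeting.
- **Non-response.** The non-response analysis in the Discussion concerns who chooses to take part and the programme's reach. It does not concern missing follow-up.

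**The concern.** An analysis of (co)variance or an ordinary regression, run as named, uses only participants with an observed outcome. It has no way to let a T1 score speak for a missing T2 score. If adjustment is made only when imbalance is seen, it need not condition on baseline PAID either.

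That would matter little if follow-up were nearly complete or loss were unrelated to distress. Here the plan itself allows for one participant in five to be lost. The outcome is a self-completed distress questionnaire, participants know which arm they are in, and the two arms carry very different attendance demands. Someone in the intervention arm who finds the programme unhelpful or burdensome may both stop returning forms and score worse. The comparison among those who respond would then favour the intervention somewhat.

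The scheduled T0, T1 and T2 scores could reduce this problem, but no method named in the article uses them jointly.

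**Working it through.** **Inputs from the Sample size section:** δ = 10 PAID points, σ = 20, two-sided α = 0.05 (z = 1.96), power 80% (z = 0.84), 76 per arm, 152 in total, 20% attrition.

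**Step 1. Reproduce the plan's figure.** n per group = (1.96 + 0.84)² × 2 × 20² / 10² = 7.84 × 8 = 62.72, rounded up to 63. This agrees with the article. The 76 per arm corresponds to 63 × 1.20 = 75.6. (Dividing by 0.80 would give 79; that is a separate matter and does not affect this point.)

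**Step 2. Numbers left at the planned attrition.** Lost: 152 × 0.20 = 30.4. Remaining: 152 × 0.80 = 121.6, or 60.8 per arm.

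**Step 3. Power.** The standard error of the difference is 20 × √(2/60.8) = 3.6 points. Power for a 10-point difference is 78.7%, against 80% planned. Precision is barely affected, so the issue is possible bias.

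**Step 4. Bias under a simple model (assumptions, not figures from the documents).** Suppose those lost, a share q of an arm, would score D points higher (worse) than those retained in the same arm. The mean among those retained is then the full-arm mean minus D × q. The bias in the difference, intervention minus control, is −D × (q_int − q_ctl). A negative value favours the intervention, because higher PAID scores mean more distress.

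| Loss, intervention vs control (20% overall) | Bias with D = 10 | Share of the 10-point target |
|---|---|---|
| 20% vs 20% | 0 | 0% |
| 25% vs 15% | −10 × 0.10 = −1.0 | 10% |
| 30% vs 10% | −10 × 0.20 = −2.0 | 20% |

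Against the standard error of 3.6, these shifts are about 0.28 and 0.55 standard errors.

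**Step 5. A second route.** Step 4 uses the same D in both arms. Suppose instead that loss is 20% in each arm, but the arm difference among those lost departs from that among those retained by 5, 10 or 20 points. The estimate is then off by 0.20 × 5 = 1, 0.20 × 10 = 2 or 0.20 × 20 = 4 points. Equal loss therefore gives zero bias only under the simple formula.

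**Step 6. What the named methods assume.** A comparison without covariates needs missingness unrelated to PAID within each arm. Baseline-adjusted analysis of covariance is valid if missingness depends only on arm and baseline. A likelihood-based model of T0, T1 and T2 also allows a missing T2 score to depend on the observed T1 score, which is a weaker requirement. The gain is largest if the treatment difference is read at T2. At T1 it is smaller, since most of those missing T1 would contribute only T0.

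**The case against.** A reader might infer that the article's intention-to-treat analysis is in truth complete-case, with a separate model at each time that discards 20% of participants. The documents do not support that.

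- **No deletion rule is stated.** The article is a condensed account, and missing-data handling is commonly left to a full protocol or SAP, which is not shown. Regression and analysis of covariance can be run on imputed data.
- **Time-by-time modelling is not stated.** The methods are to be applied, in the article's words, so that "linear and logistic regression will be used to determine the effect of the intervention on each of the outcome measurements". That can equally mean each outcome instrument.
- **The 20% is overall attrition,** not a missing rate for each questionnaire.
- **The label is not misused.** Intention-to-treat is set against the per-protocol set, so it means analysis by assigned arm whatever the attendance. Missing outcomes do not contradict that.
- **The attrition allowance proves nothing about deletion.** Recruitment is inflated whatever the missing-data method. Nor does a 20% loss leave the required 63 per arm; it leaves about 61.
- **People seen at T1 but not T2 are not wasted.** They still count in any T1 comparison.
- **The bias is assumed and modest.** No figure in the article supports 10 points or unequal loss, and baseline adjustment, which the named methods permit, would remove part of it.

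All of this stands. It removes the charge of mislabelling and the claim that participants will certainly be dropped. It does not remove a narrower point: the article does choose its methods, and for scores already scheduled at three times a better choice exists that costs only analysis work.

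**Conclusion.** The point holds as an inexpensive improvement to a stated choice of method, not as an error in the intention-to-treat label. Unless something further is specified, the named methods leave out participants with a missing PAID score and do not use T0 and T1 to inform T2, in a trial that allows for about 30 of 152 to be lost and has unequal burden between arms.

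Under the simple formula, with those lost scoring 10 points worse, the bias is 0 at equal loss, 1 point at 25% against 15%, and 2 points at 30% against 10%. Both the 10 points and the loss patterns are assumptions, so these figures show a plausible scale and do not predict the actual bias. Power is hardly affected.

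**What to change.** Make the primary PAID analysis a longitudinal linear mixed model that includes every randomised participant with at least one PAID score:

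- T0, T1 and T2 scores as outcomes, with a common mean at T0 for both arms;
- arm-by-time effects at T1 and T2;
- unstructured within-person covariance;
- the treatment difference, with its 95% confidence interval, read at the primary time point, named in advance.

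Add one sensitivity analysis: impute PAID for those lost and add 0 to 10 points to the imputed values in the intervention arm. If 20% of that arm is lost, the full 10 points moves the difference by 0.20 × 10 = 2.0 points. Report whether the conclusion changes over the range.

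The cost is a change of analysis wording and slightly more modelling, with no new data or visits. The drawback is that the mixed model relies on missing-at-random, which the data cannot verify; the sensitivity analysis is there to probe it.

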### Peer leaders and group psychotherapists

The peer leader leads the group to share experiences and give advice, and to encourage each other to be proactive regarding his or her diabetes care. All eight recruited peer leaders were diagnosed with diabetes over ten years ago. They have worked for the Dutch Diabetes Association and have had at least five years of experience working as a diabetes educator. Following recruitment, the peer leaders completed one day of training. The training included an introduction to the study; the role of the peer leader and its limitations (i.e. not being a medical doctor); communication and role-playing to practice handling difficult situations. In addition to the training, peer leaders are supported during the intervention period by means of monthly phone calls after each session with a member of the research team.

During the group meetings, the peer leaders are supported by a group psychotherapist. The peer leader and the group psychotherapist form a team. The role of the group psychotherapist is to manage group dynamics and help the peer leader to stimulate interaction between the participants. The four group psychotherapists were recruited through the network of the research team. Like the peer leaders, the group psychotherapists received training on their role in the intervention. They were also instructed to fill out a form to evaluate each peer group session (i.e. which forms of peer support were observed).

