## Discussion

Peers support is a way for patients to stay motivated and help each other to deal with the stress T2DM often brings. This article contains a description of the design of a study that will investigate the effect of a group-based, peer support intervention on diabetes distress in patients with T2DM.

As previously stated, there is limited and inconsistent evidence on the effect of peer support on diabetes outcomes in adults with T2DM [10]. This trial will deliver important additional insight into the effects of peer support on patient-important outcomes like diabetes distress. To increase the effectiveness of our peer support intervention, the design is based on the MRC Framework [11] and on the social support model [7]. Both frameworks will contribute to the interpretation of the final results and will facilitate the reproducibility of our unique intervention, led by both voluntary laypersons with T2DM and group psychotherapists.

The actual delivery of the intervention may highlight some limitations, however. Concerns may arise regarding the dependence on (and the difference in) the knowledge and skills of the peer leaders and group psychotherapists. Training ensures that peer leaders and group psychotherapists are familiar with the dimensions of peer support and are capable of judging whether or not all dimensions are dealt with during the group sessions. Another concern may be the self-selection of participants as a potential threat to external validity. Because little is known about T2DM patients who take part in (peer) group interventions, we plan to conduct a non-response analysis and describe the reach of our programme.

To conclude, the present study will evaluate the effects of a group-based, peer support intervention led by a peer leader and group psychotherapist on diabetes-related distress, well-being and health-related quality of life, self-management behaviour, and perceived social support in patients with T2DM. Our findings will contribute to knowledge in the field of peer support and T2DM.

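### Sample size and named analyses treat participants as independent although the intervention is delivered in peer groups; the cost in power and type I error depends on an ICC and group size that the article does not give

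*Protocol article*

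**What the plan says.** The Patients and practices section randomises individual patients. Under Intervention, the active arm attends six monthly two-hour group sessions, and exchange and discussion among participants is named as an essential part. Under Peer leaders and group psychotherapists, "The peer leader and the group psychotherapist form a team"; there are eight peer leaders and four psychotherapists in all. Under Control group, controls are invited to one educational meeting.

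The Sample size section prints the two-group formula for independent observations, with two-sided alpha 0.05, 80% power and a difference of 10 points. It takes the scatter from earlier data, where "the standard deviation (SD) of PAID (scores transformed to 0-100) was 20 points". The result is given as "This leads to a sample size of 63 per group", raised to 76 per arm (152 in total) for 20% attrition. No group size, ICC or design effect appears.

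The Analyses section states: "Analysis of (co)variance, linear and logistic regression will be used to determine the effect of the intervention on each of the outcome measurements". No group or leader term, mixed model or robust standard error is mentioned. The Discussion adds: "Concerns may arise regarding the dependence on (and the difference in) the knowledge and skills of the peer leaders and group psychotherapists", and answers this with training.

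**The concern.** People who share a group and its leaders over six months, in a programme built on mutual exchange, are likely to have correlated outcomes. Controls, with one meeting, are close to independent. Correlation in one arm inflates the variance of that arm's mean. A formula or regression that assumes independence misses this inflation, so the standard error of the treatment effect is too small.

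Three things follow if the ICC is positive: the power is overstated, the nominal 5% test rejects too often, and the 95% intervals cover less than 95%. The error favours a false positive finding. It touches the primary PAID comparison and every secondary outcome analysed the same way.

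**Working it through.** **Inputs from the Sample size section:** difference 10, SD 20, two-sided alpha 0.05 (z = 1.96), power 80% (z = 0.84), 63 evaluable per arm, 20% attrition, 76 per arm recruited.

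**Assumptions, not in the article:** ICC 0.01 to 0.10, and m = 6 to 12 evaluable members per group. The only group size in the article is six, from the single pilot meeting.

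**Step 1, the article's own figure.** (1.96 + 0.84)² × 2 × 20² / 10² = 62.7, rounded up to 63. This reproduces. Power at 63 per arm is 80.1%.

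**Step 2, clustering in the intervention arm only.**
- Design effect: DE = 1 + (m − 1) × ICC
- True standard error: SE = 20 × √(1/63 + DE/63)
- Power = Φ(10/SE − 1.96)
- Standard error assuming independence: SE₀ = 20 × √(2/63) = 3.56
- True level of the nominal 5% test = 2 × [1 − Φ(1.96 × SE₀/SE)]; interval coverage is one minus this.

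*Example, m = 8 and ICC 0.05:* DE = 1 + 7 × 0.05 = 1.35. SE = 20 × √(2.35/63) = 3.86. Power = Φ(2.59 − 1.96) = Φ(0.63) = 73.5%. SE/SE₀ = 1.084, so the true level is 7.1% and coverage 92.9%.

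Range, each cell running from m = 6 to m = 12:

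| ICC | DE | Power at 63 per arm | True level | Coverage of 95% CI |
|---|---|---|---|---|
| 0.01 | 1.05 to 1.11 | 79.2% to 78.0% | 5.3% to 5.6% | 94.7% to 94.4% |
| 0.02 | 1.10 to 1.22 | 78.2% to 75.9% | 5.6% to 6.3% | 94.4% to 93.7% |
| 0.05 | 1.25 to 1.55 | 75.4% to 70.0% | 6.5% to 8.3% | 93.5% to 91.7% |
| 0.10 | 1.50 to 2.10 | 70.9% to 61.6% | 8.0% to 11.5% | 92.0% to 88.5% |

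These are normal approximations. They ignore the few degrees of freedom that come with a small number of groups, so a valid test would have somewhat less power than shown.

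**Step 3, attrition kept apart.** The 76 per arm equals 63 × 1.2 = 75.6, rounded up; 63/0.8 would be 79. With 20% loss, 76 × 0.8 = 60.8 remain, and power is 78.7% with no clustering at all. Those 1.4 points (80.1 − 78.7) are a separate matter. With both effects, power at 152 participants is 77.7% to 76.5% at ICC 0.01, 73.9% to 68.5% at ICC 0.05, and 69.4% to 60.0% at ICC 0.10 (m = 6 to 12).

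**Step 4, baseline adjustment.** Assume a baseline correlation of 0.5, 60.8 completers per arm, ICC 0.05 and m = 7.6 (76/8 × 0.8, as if there were eight groups). DE = 1 + 6.6 × 0.05 = 1.33.
- If baseline reduces group and individual variance alike: SD = 20 × √0.75 = 17.3, SE = 17.3 × √(2.33/60.8) = 3.39, power about 84%.
- If it explains only individual variation: the group variance stays at 0.05 × 400 = 20 out of 300, so the ICC becomes 0.067, DE = 1.44, SE = 3.47, and power about 82%.

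**The case against.** The strongest reply is that the loss is not established. The article gives no ICC and no trial group size, and at ICC 0.01 the loss is 1 to 2 points, with coverage still above 94%. That stands: the direction is certain for any positive ICC, the amount is not.

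Second, this is a condensed article. A one-sentence list of model families does not rule out a group term or cluster-robust errors in a fuller analysis plan. That weakens the analysis half of the point. It does not touch the Sample size section, where the formula and its result are fixed and assume independence.

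Third, analysis of covariance is listed, and the abstract treats 152 as a minimum, so actual power may reach 80%. That is possible, but the Analyses section does not name baseline PAID as a covariate, and ordinary ANCOVA without a group term would still understate the standard error.

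A reader might also infer more than the text supports:
- that there is one group per peer leader, hence eight groups. The article does not say this.
- that leader teams are expected to differ. The Discussion raises it only as a possible concern and offers training as the answer.
- that the whole shortfall from 80% at 152 participants is due to clustering. Part of it is the attrition step.

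**Conclusion.** The point holds in conditional form. The design is partially nested, and neither the sample-size formula nor the named analyses account for it. Because 63 per arm leaves no reserve, the power statement as calculated is true only if the ICC is zero. The ranges in the table rest on assumed ICCs and group sizes, on clustering in one arm only, and on a normal approximation.

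A reader might conclude outright that the trial will miss 80% power and that its intervals will be materially too narrow. The article does not support that: a very small ICC would make the effect minor, and a baseline-adjusted analysis could restore the power. The inflated type I error would remain for any positive ICC unless the group is modelled.

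**What to change.** **Analyses section.**
- Analyse PAID with a partially nested linear mixed model: a random intercept for peer group in the intervention arm only, arm-specific residual variance, and Satterthwaite or Kenward-Roger degrees of freedom.
- Use the same structure for continuous secondary outcomes. For binary ones use a clustered logistic equivalent, with either a random group effect or cluster-robust errors with a small-sample correction.
- Examine peer leader or psychotherapist as a sensitivity analysis, and report the estimated ICC.

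**Sample size section.** State the planned group size and restate the power at 152 participants over an assumed ICC range of 0.01 to 0.10, with the attrition shortfall reported separately. If baseline PAID is named as a covariate, its gain can be shown with the assumed correlation; it does not replace the group term.

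**Cost.** Changed wording and a restated power figure, with no extra patients; group membership will be known from running the sessions. The intervals become slightly wider and the power figure less favourable. The group identifier reveals the arm, while the article wants allocation hidden from the analyst, so the code should be finalised on dummy allocations first.

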## Discussion

Peers support is a way for patients to stay motivated and help each other to deal with the stress T2DM often brings. This article contains a description of the design of a study that will investigate the effect of a group-based, peer support intervention on diabetes distress in patients with T2DM.

As previously stated, there is limited and inconsistent evidence on the effect of peer support on diabetes outcomes in adults with T2DM [10]. This trial will deliver important additional insight into the effects of peer support on patient-important outcomes like diabetes distress. To increase the effectiveness of our peer support intervention, the design is based on the MRC Framework [11] and on the social support model [7]. Both frameworks will contribute to the interpretation of the final results and will facilitate the reproducibility of our unique intervention, led by both voluntary laypersons with T2DM and group psychotherapists.

The actual delivery of the intervention may highlight some limitations, however. Concerns may arise regarding the dependence on (and the difference in) the knowledge and skills of the peer leaders and group psychotherapists. Training ensures that peer leaders and group psychotherapists are familiar with the dimensions of peer support and are capable of judging whether or not all dimensions are dealt with during the group sessions. Another concern may be the self-selection of participants as a potential threat to external validity. Because little is known about T2DM patients who take part in (peer) group interventions, we plan to conduct a non-response analysis and describe the reach of our programme.

To conclude, the present study will evaluate the effects of a group-based, peer support intervention led by a peer leader and group psychotherapist on diabetes-related distress, well-being and health-related quality of life, self-management behaviour, and perceived social support in patients with T2DM. Our findings will contribute to knowledge in the field of peer support and T2DM.

